**Results:**

The study got underway in April 2024. Since participants may begin at any time, our goal is for everyone to be finished by May 2025.

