#### Secondary Objectives

The secondary objectives are (1) to evaluate the residual efficacy of Navak Guggulu versus Vachaharidradi Gana Vati in children with Sthaulya (overweight) after discontinuation of treatment after 180 days as well; (2) to study the effect of desha, kala, and prakruti on the children with overweight; and (3) to study the adverse effects of Vachaharidradi Gana Vati if any.

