## Methods

### Study Design

A randomized, standard-controlled, double-blind equivalence clinical trial will be performed. The study flow is depicted in Figure 1. The study participants required for the trial include children with overweight aged between 10 and 16 years of age will be selected from the Outpatient Department and Inpatient Department of the Department of Kaumarbhritya, Mahatma Gandhi Ayurveda College Hospital and Research Centre, Salod (H), and Chhatrapati Shahu Maharaj Shikshan Sanstha’s (CSMSS) Ayurved College and Hospital, Chhatrapati Sambhajinagar, based on the inclusion criteria.

Overweight (Sthaulya) children will be diagnosed as having a BMI greater than or equal to 23 and less than 27 kg/m^2^ [11]. Screening will include hemoglobin percentage, thyroid-stimulating hormone, and random blood sugar. A total of 88 diagnosed children with overweight will be selected after obtaining written informed consent from their guardians. Participants will be randomly divided into 2 groups by block randomization using a computerized random number generator or statistical software. Group A (control group) will receive Navak Guggulu, while group B (trial group) will receive Vachaharidradi Gana Vati orally (Table 1). Medications will be dispensed in opaque containers following the sequentially numbered, opaque, sealed envelope (SNOSE) technique to maintain allocation concealment. Both groups will receive counseling to perform 12 Suryanamaskara (Sun Salutation) per day and adhere to the dietary restrictions. Guardians will be educated and advised to support their children’s consistent participation in the interventions. All the baseline parameters will be recorded at the study’s initiation. The treatment duration will be 90 days, with follow-up assessments on the 15th, 30th, 45th, 60th, 75th, and 90th day to monitor progress and ensure adherence. Lipid profile will be assessed before treatment and on the 90th day of intervention to evaluate the efficacy of the interventions. An additional follow-up will occur on the 180th day to determine whether the intervention’s possible effects are lasting.

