#### Subjective Parameters

Signs and symptoms of obesity (Sthaulya) are mentioned in the Ayurvedic texts, and for assessing the severity of each symptom, they were graded following the book called WHO-Direct Financial Cooperation sponsored project on Developing Guidelines for Clinical Research Methodology in Ayurveda. It is illustrated in Table 4 [43].

**Table 4 table4:** Signs and symptoms of Sthaulya according to Ayurvedic classics.

Signs and symptoms or gradation	0	1	2	3	4
Pendulous hips, abdomen, breasts (chala sphika, udara, stana)	Absence of movements (in the areas) (Chalatva)	Little visible movement (in the areas) after rapid movement	Little visible movement (in the areas) after moderate movement	Movement (in the areas) after mild movement	Movement (in the areas) after changing posture
Bad odor (angagandha)	No odor	Bad odor but not offensive	Strong odor but can be lessened by the use of deodorants and perfumes	Very strong odor even after using fragrances (use of deodorants or perfumes)	—^a^
Perspiration (swedadhikya)	Sweating after heavy work and fast movement or in hot weather	Profuse sweating after moderate work and movement	Sweating after little work and movement (stepping ladder)	Profuse sweating after little work and movement	Sweating even at rest or in cold weather
Increased appetite (kshudha-adhikya)	As usual or routine	Slightly increased (1 meal extra with routine diet)	Moderately increased (2 meals extra with routine diet)	Markedly increased (3 meals extra with routine diet)	—
Increased thirst (pipasa-adhikya)	Feeling of thirst (7-9 times or 24 hours) and relieved by drinking water	Feeling of moderate thirst (>9-11 times or 24 hours) and relieved by drinking water	Feeling of excess thirst (>11 times or 24 hours) and not relieved by drinking water	Feeling of severe thirst (>13 times or 24 hours) and not relieved by drinking water	—
Exertional dyspnea (kshudra shwasa)	No dyspnea even after heavy work	Dyspnea after moderate work but relieved later and tolerable; dyspnea by climbing upstairs of 10 steps, and time taken will be more than 15 seconds	Dyspnea after little work but relieved later and tolerable; dyspnea by climbing upstairs of 10 steps, and time taken will be more than 25 seconds	Dyspnea after little work but relieved later and not tolerable; dyspnea by climbing upstairs of 10 steps, and time taken will be more than 35 seconds	Dyspnea in resting condition

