### Statistical Analysis

The statistical analysis will be performed at the end of the study. It will involve various tests to evaluate both within-group and between-group efficacy of Navak Guggulu and Vachaharidradi Gana Vati in managing Sthaulya (overweight) among children. For normally distributed continuous variables like BMI, WHR, and skinfold thickness, paired 2-tailed *t* tests will be used to evaluate the efficacy of each intervention within the same group (pre- and posttreatment comparisons).

For nonnormally distributed data, the Wilcoxon signed rank test will be used. For normally distributed data, independent 2-tailed *t* tests will be used for between-group comparisons of mean changes; for nonnormal data, the Mann-Whitney *U* test will be used.

To ensure valid comparisons, the analysis of covariance will be used to account for any potential baseline variations between groups. To evaluate residual efficacy after treatment discontinuation at 180 days, repeated measures ANOVA will analyze longitudinal changes in outcomes, while mixed-effects models will handle missing data or variability across time points. For stratified analysis based on Desha (geography), Kala (season), and Prakruti (body constitution), multivariate regression analysis will identify predictors of treatment efficacy, and interaction analysis will explore the influence of these factors. A statistician consultation will be considered for the selection of the proper statistical method.

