
## Results

In April 2024, the randomized controlled study got underway. Since participants may be in the study at any time, our goal is to complete the research by May 2025. Any significant changes to the protocol will be posted on ClinicalTrials.gov. The study’s findings will be disseminated through publications.

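### Baseline and follow-up visits fall in different seasons, so within-arm change in the weather-graded perspiration item is confounded with season, and Kala should be coded by visit date

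*Protocol article*

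**What the plan says.** Timing. The Abstract gives the calendar: "The study got underway in April 2024. Since participants may begin at any time, our goal is for everyone to be finished by May 2025". The Results section repeats the target: "our goal is to complete the research by May 2025". Under Study Design, "The treatment duration will be 90 days, with follow-up assessments on the 15th, 30th, 45th, 60th, 75th, and 90th day", and a further visit follows on day 180.

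Season. Secondary objective 2 is "to study the effect of desha, kala, and prakruti on the children with overweight". The Statistical Analysis section takes this up: "For stratified analysis based on Desha (geography), Kala (season), and Prakruti (body constitution), multivariate regression analysis will identify predictors of treatment efficacy", with an interaction analysis of the same three factors. Kala is glossed only as season. No list of seasons, cut dates or visit of assignment is given.

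Symptoms. Table 4 (Subjective Parameters) grades perspiration from 0 to 4. Grade 0 includes sweating in hot weather, and grade 4 reads "Sweating even at rest or in cold weather". Thirst is graded by episodes per 24 hours, with no reference to weather. Reduction in these signs and symptoms is a secondary outcome.

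Tests. Efficacy within each arm is evaluated by paired before-after comparison: a t test, or, "For nonnormally distributed data, the Wilcoxon signed rank test will be used". Primary objectives 1 and 2 concern each arm's own effect on BMI and other parameters, so within-arm results are meant to be read as evidence. Between-arm tests and mixed-effects models are also planned.

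**The concern.** A before-after test attributes to treatment whatever changes between the two visits. When nearly all children start in one part of the year and are re-measured in another, season is one of those changes, and neither arm goes without a study tablet to show its size. This matters most for an outcome whose grades are worded in terms of weather. A within-arm statement that perspiration fell, or did not fall, would then be uninterpretable as drug efficacy.

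Kala raises a related problem. It is listed beside Prakruti, which is an attribute of the child, but season changes during each child's own treatment. A season factor that does not say which date it refers to cannot be interpreted as a predictor of a 90-day or 180-day response.

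**Working it through.** The article gives no figure to reproduce, so the check is a calendar count.

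**Inputs from the article:** start in April 2024; completion by May 2025; 90 days of treatment; last visit on day 180.

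**Assumptions:** first entry on 1 April 2024; even enrolment; completion between 1 and 31 May 2025; seasons of 2, 3, 4 or 6 months, because the article defines none.

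**Step 1. Last possible entry** = completion date minus 180 days.
- 1 May 2025 minus 180 days = 2 November 2024, an entry window of 216 days.
- 31 May 2025 minus 180 days = 2 December 2024, a window of 246 days.

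**Step 2. Where the visits fall** (216-day window / 246-day window).

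| Months | Baseline | Day 90 | Day 180 |
|---|---|---|---|
| April-September | 85% / 74% | 43% / 38% | 16% / 26% |
| November-February | 1% / 13% | 43% / 49% | 56% / 49% |
| December-March | 0% / 1% | 29% / 37% | 56% / 49% |

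For example, 183 of the 216 possible entry dates lie in April to September (183/216 = 85%), but only 34 of the 216 day-180 dates do (34/216 = 16%). The seasonal shift therefore runs the same way for most children and does not average out across them.

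**Step 3. Season change per child.** Let S be the season length in days, with entry spread evenly over the season.
- For S of 90 or more, the share whose day 90 lies in another season is 90/S. For S = 91.5, 122 and 183 this is 98%, 74% and 49%. For S = 61 it is 100%.
- The share whose day 180 lies in another season is 180/S for S = 183, which is 98%, and 100% for shorter seasons.

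Counting actual dates in both windows and varying the month in which seasons begin gives, for baseline versus day 90, 100% (2-month), 97-99% (3-month), 70-83% (4-month) and 37-61% (half-years). An unequal four-season calendar (2, 3, 4 and 3 months) gives 84-86%. Baseline versus day 180 differs for about 98% or more under every calendar.

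**Step 4. Treatment time outside the entry season.** If a child is labelled by season at entry, the mean share of the 90 days outside that season is 1 - S/180 for S up to 90, and 45/S for longer seasons.

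| Season length | Formula | Date count, both windows |
|---|---|---|
| 2 months (S = 61) | 1 - 61/180 = 66% | 63-68% |
| 3 months (S = 91.5) | 45/91.5 = 49% | 44-53% |
| 4 months (S = 122) | 45/122 = 37% | 30-41% |
| 6 months (S = 183) | 45/183 = 25% | 18-34% |

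If the label were instead the season covering most of a child's treatment, the share outside falls to 36-37% (six seasons), 21-24% (four), 18-19% (three) and 11-14% (two).

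**Step 5. Direction for perspiration.** Sweating in hot weather is already grade 0, so a child who sweats only in heat has nothing to lose by entering in summer. The cold-weather criterion for grade 4 can be met only when it is cold, which could raise grades later in the year. Grades 1 to 3 are defined by exertion, and cooler months might lower them. The wording allows movement either way.

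**The case against.** The strongest reply is that the article never says each child receives one season label. It plans regression, interaction analysis and mixed-effects models, collects data every fortnight, and may leave coding to a fuller document. That stands: a reader might infer a fixed label from the listing beside Prakruti, but it is not stated. Season at entry would also be a legitimate covariate; it would simply answer a narrower question than season during treatment.

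A reader might also infer that a label misclassifies most treatment time. That holds clearly only for 2-month seasons labelled at entry. It is about half for 3-month seasons and less than half for longer ones.

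Two further inferences are not supported. One is that before-after tests would credit cooler months to the tablets; Step 5 shows that the direction is open. The other is that the thirst grades shift with the weather. That is plausible, but those grades do not mention weather.

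Nor is winter unobserved: about half of the day-180 visits fall in November to February. What is missing is winter entries. May 2025 is also a goal, and later completion would widen the entry window and weaken the one-directional shift. The season change between baseline and day 180 for an individual child would remain, because it follows from the 180-day interval.

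Finally, the scope is small: one of seven symptom items and one secondary objective. None of this removes the confounding in the planned within-arm perspiration test, which the article does state.

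**Conclusion.** The point holds in limited form. On the article's own dates, baseline and day 180 fall in different seasons for nearly every child, and baseline and day 90 do so for most children if seasons last 2 to 4 months. For perspiration, whose grades name hot and cold weather, the within-arm before-after test cannot separate treatment from season, and the sign of the distortion is unknown. For Kala, the factor varies within each child's treatment and its reference date is not given. If it is taken at entry, a substantial part of treatment time lies outside it and almost no children enter in December to March.

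The figures assume even enrolment from 1 April 2024 and completion during May 2025; season lengths are also assumed.

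A reader might extend this to the comparison between drugs. The documents do not support that. Blocks of 4 keep the arms recruiting together, never more than two children apart in the allocation sequence, so a common seasonal shift largely cancels. The primary between-arm BMI comparison is not affected.

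**What to change.** In the Statistical Analysis section:

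1. Base conclusions on perspiration on the concurrent between-arm comparison, and report its within-arm change as descriptive only.
2. Define the seasons used for Kala, code season from each visit date, and enter it as a time-varying term in the mixed-effects model already planned.
3. Label the Kala results exploratory and limited to the seasons and visits actually covered, noting the near absence of December to March entries.

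Adjustment for month of enrolment is not needed, because the blocks already balance calendar time.

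The cost is wording and some analysis time. No visits or measurements are added; only the visit dates are needed. The price is one fewer within-arm efficacy claim and a more cautious Kala statement. With 88 children, and season only partly separable from visit, season-by-arm estimates will be imprecise, which is a further reason for the exploratory label.

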### Data Monitoring Committee

It consists of the researcher, under the guidance of the supervisor and cosupervisor, along with the statistician and departmental faculty members. The progress will be monitored by supervisors and statisticians by reviewing the group-wise case record forms and master charts.

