#### Allocation Implementation

To maintain allocation concealment, the group assignments will be placed in SNOSE, with each envelope containing 1 allocation based on the pregenerated sequence. The SNOSE technique is widely used in clinical trials [46]. The process of assigning treatments to these envelopes will be conducted by personnel not involved in enrolling or assessing participants. To maintain blinding, treatments will be labeled with coded identifiers. Treatments A and B will be recoded by unblinded, trained faculty using either code III or code IIII. This unblinded faculty will not be involved in the trial’s conduct and assessment. The blind code III or IIII will be labeled on the respective patient numbers on the opaque containers by the trained, unblinded faculty. These recoded opaque containers will then be handed over to the investigator for further administration to the patients. An unblinded, trained faculty will also provide 88 sealed envelopes to the investigator, containing unblinded information about the treatment administered to each patient. These sealed envelopes will be kept intact under the investigator’s custody until the completion of the last visit of the last enrolled patient in the study and stored in a manner that prevents accidental disclosure. A master chart will be prepared as a data source for statistical analysis and will be handled with high security, ensuring confidentiality and limited access to authorized personnel only. When the data have been locked, the outcome assessor (statistician) will unblind the treatment codes for statistical analysis.

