### Ethical Considerations

The Mahatma Gandhi Ayurved College Hospital and Research Centre’s Institutional Ethics Committee approved this study (registration: MGACHRC/IEC/July-2022/521), and it was also registered with the Clinical Trial Registry of India (CTRI/2023/03/051135). The same ethical committee also approved the addition of the site at CSMSS Ayurved College, Chhatrapati Sambhajinagar. After receiving a No Objection Certificate from the institutional ethical committee of the CSMSS Ayurved College (AMCS/1407/2023), the participant recruitment at both sites will be initiated. The institutional ethical committee will decide on the end point and oversee the trial as it progresses. The researchers will assess any adverse events and will report to the ethics committee. Consent from parents and assent from patients (older than 12 years) will be obtained before conducting the trial in the local language while explaining every aspect of the study. Every participant will get information regarding the study’s design and objectives, data confidentiality, and the freedom to withdraw from the study at any moment without giving a reason. The informed consent form includes a patient information sheet (part 1) and a certificate of consent (part 2). Secondary analysis will be covered without additional consent. Data will be anonymized, and the personal information of the participants will be kept confidential before, during, and after the trial. Physical data will be stored in a protected storage facility, with access available only to the researchers. Computerized data will be held in a password-protected computer. Data access will be restricted to members of the research team only. During data analysis, measures will be taken to protect participants’ privacy. Participation in the study is completely voluntary; hence, no incentive will be provided to the participants. During the treatment period, if the patients’ condition worsens, the case will be excluded and will receive conventional treatment and care until the symptoms subside, free of charge. The ethics committee will be informed of the patient’s condition. The therapy will be discontinued, and the child will be withdrawn from the study if any other illness arises during the treatment period that could influence study outcomes. Similarly, if a participant experiences personal issues that prevent continuation of therapy and are likely to affect the study results, they will also be withdrawn. If the patient misses any of the periodic follow-ups during the intervention, they will be excluded from the study.

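### Group-wise review of trial records by the study team is not reconciled with the double-blind design or with opening the codes only after data lock

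*Protocol article*

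**What the plan says.** The protocol article's Study Design section sets the standard: "A randomized, standard-controlled, double-blind equivalence clinical trial will be performed".

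Allocation Implementation explains how the blind is kept. On coding: "Treatments A and B will be recoded by unblinded, trained faculty using either code III or code IIII". On where the code appears: "The blind code III or IIII will be labeled on the respective patient numbers on the opaque containers by the trained, unblinded faculty". The containers then go to the investigator. On the data: "A master chart will be prepared as a data source for statistical analysis", with access limited to authorized people. On unblinding: "When the data have been locked, the outcome assessor (statistician) will unblind the treatment codes for statistical analysis".

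The Data Monitoring Committee section gives the membership: "It consists of the researcher, under the guidance of the supervisor and cosupervisor, along with the statistician and departmental faculty members". It then describes the monitoring: "The progress will be monitored by supervisors and statisticians by reviewing the group-wise case record forms and master charts".

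Three other sections bear on the point:
- Data Collection Tools and Process puts the objective measurements and the symptom grades into the case record forms every fortnight for 90 days.
- Statistical Analysis places the analysis at the end of the study. It leaves the final selection of method open to later advice from a statistician.
- Ethical Considerations lists several grounds for taking a child out of the study after randomization. It also says: "The institutional ethical committee will decide on the end point and oversee the trial as it progresses".

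**The concern.** The blinding section closes the codes until lock, while the monitoring section has members of the study team read the records by group as the trial runs. Neither section refers to the other.

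Monitoring progress does not need a split by group. Recruitment, visit completion and data quality can all be judged on pooled records. The split adds only comparative information, which a double-blind design is meant to keep from the team until lock.

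What is at stake is conduct and analysis. People who can see which group is doing better may, without intending to, be influenced in decisions that the article leaves to discretion.

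**Working it through.** No figure in the plan bears directly on this point, so the check sets the sections side by side.

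1. **What the reviewed records contain.** The master chart is the source for the statistical analysis (Allocation Implementation). The case record forms hold the fortnightly objective measurements and symptom grades (Data Collection Tools and Process). BMI is the primary outcome (Outcomes). The review therefore covers accumulating efficacy data as well as administrative records.

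2. **When.** The stated purpose is to follow progress, so the review takes place while the trial is running and before lock.

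3. **Who.** The review is assigned to supervisors and statisticians. The committee to which they belong consists of the researcher, supervisor, cosupervisor, statistician and departmental faculty. No member from outside the team is named.

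4. **What 'group-wise' can mean.** The article does not define it, and there are two readings.
   - *True arm.* The reviewers know the allocation before lock. This contradicts the rule that codes are opened only after lock, and the blind is broken for those reviewers.
   - *Code III or IIII.* The allocation stays nominally hidden. However, there are 88 children and two fixed codes, so 88 / 2 = 44 children share each code. Records sorted by code show the between-group difference as it develops, without a name on either group. If the treatment of one child becomes known, all 44 with that code are known, and the other 44 follow by elimination.

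   Neither reading fully agrees with the blinding section.

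5. **Which decisions are open to influence.** Ethical Considerations allows a child to be excluded when the condition worsens. It also allows withdrawal for another illness or for personal reasons judged to bear on the results. These involve judgement. Statistical Analysis leaves the choice of method partly open, and a statistician is among those who see the grouped data.

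6. **Effect on type I error.** A calculation would need a number of looks and a rule for declaring a result or stopping at a look. The article gives neither and describes one analysis at the end. With no test and no decision at the reviews, the error rate stays at its nominal level, so no inflation figure is offered.

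**The case against.** The strongest reply is that the article protects the blind carefully and the monitoring sentence should be read in that light. Containers are opaque and coded, envelopes are sealed, and codes are opened after lock. On that reading 'group-wise' means by code, for a review of progress only. This is a fair reading, and it rules out saying outright that the blind is broken. It does not remove the point, because sorting by two fixed codes still shows the team comparative data.

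A reader might also infer more than the article supports:
- *That there are uncontrolled interim analyses which raise the false-positive rate.* The analysis is placed at the end, and no interim test, boundary or stopping on a look is described. The ethics committee decides on the end point, but nothing says it receives efficacy data by group.
- *That the reviewers are the same people who counsel families, grade symptoms or judge worsening.* The article gives assessment to trained observers and does not name who counsels or who judges worsening.
- *That the unblinded faculty member sits on the committee.* Departmental faculty are members, but the person holding the allocation is said to be outside the study. The article does not say whether the two overlap.

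Two further replies have some force. Nothing in the article requires an independent committee, so in-house membership alone is not an error; it matters because of what the members are shown. And since the investigator receives containers marked III or IIII, the team could sort records by code whatever the monitoring section says. New wording therefore lowers the risk but does not remove it.

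That this is a condensed article does not answer the point, because the group-wise review is a stated procedure and not an omitted detail.

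**Conclusion.** The point holds as an unreconciled conflict between sections. Group-wise review by the study team before lock does not fit the double-blind design or the rule on when codes are opened. Under the true-arm reading the reviewers are unblinded. Under the code reading the emerging difference is visible and the blind is fragile, since one disclosure identifies the treatment of all 88 children.

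The consequence is a risk of bias in discretionary withdrawals and exclusions and in the choice of method. Its size cannot be derived from the article. The conclusion assumes that 'group-wise' carries its ordinary meaning of separated by treatment group or code, and that the forms and master chart under review contain the outcome data that other sections assign to them. No loss of the blind is asserted as fact, and no type I error inflation is claimed.

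**What to change.** In the Data Monitoring Committee section:
- Replace 'group-wise' with 'pooled, not by group or code'.
- Limit the team's review to recruitment, visit completion and data quality.
- State that no efficacy summary by group or by code is produced before database lock.
- State that any by-group safety review goes only to people outside the study team, such as the ethics committee that already oversees the trial.

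Then reconcile this section with Allocation Implementation, including who prepares any by-group safety listing. The unblinded faculty member cannot simply be given that task, because Allocation Implementation keeps that person out of the trial's conduct and assessment.

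The cost is small: revised wording, a named preparer if by-group safety listings are wanted, and the team's loss of by-group sight of the data during the trial.
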